## Abstract

**Background:**

Pregnancy-related anxiety and depression has received considerable attention worldwide. Mental health problems in pregnant women already since early weeks of gestation may have important consequences to the fetus. The necessity for more effective health care pathways, including some early interventions that reduce the overall burden of the childbearing situation appears a key factor for a successful birth and care of the baby. The few studies focalized in interventions, are focused on delivery and postpartum, without taking into account the whole maternity process. Current literature recommends the use of interventions based on new technologies for the treatment of mood disorders, already during the prenatal period. There have been scarce well-designed intervention studies that test technological low-intensity interventions by midwives to address pregnant women’s mental health, diminishing anxiety and depression during pregnancy.

**Methods/design:**

Adult pregnant women (weeks 12–14 of gestation) will be recruited and screened from different primary care centers in Catalonia, Spain. Women who pass the initial mental screening will be randomly allocated to the relaxation virtual reality intervention or control group. The intervention aims to improve mental state of pregnant women during pregnancy, work through breathing, mindfulness and muscle relaxation techniques. Women in the control group will receive standard care offered by the public funded maternity services in Catalonia. The primary outcome measures will include the Edinburg Postnatal Depression (EPDS), State Trait Anxiety Inventory (STAI), Symptom Checklist-90 (SCL-90), and the Cambridge Worry Scale (CWS) instruments. Secondary outcome measures will include the Temperament and Character Inventory-Revised (TCI-R) and the Whooley and Generalized Anxiety Disorder-2 (GAD-2) questions. Routinary pregnancy monitoring measures will be also evaluated.

**Discussion:**

This study aims to test the efficacy of a low-intensity, midwife-led e-health intervention based on new technologies to work on women’s anxiety and depression during pregnancy. We hypothesize that low-intensity mental health intervention during pregnancy, using an e-health (virtual reality) as a support tool, will be effective in reducing of anxiety, depressive symptoms, and improving satisfaction with pregnancy follow-up.

**Trial registration:**

Clinical Trials ID NCT05756205.

**Supplementary Information:**

The online version contains supplementary material available at 10.1186/s12912-023-01440-4.

## Background

Motherhood is a normal process of life characterized not only by physiological and biological changes in the mother's body, including physical brain changes, but also by a psychological adaptation to the new reality of pregnancy, childbirth and the future baby [1–5].

The prevalence of anxiety and depression in pregnant women has significantly increased after the spread of coronavirus-19 (COVID-19) throughout the world. Anxiety related to pregnancy is relatively common, with a current prevalence COVID-related between 26%-57% of women, appearing to be a unique syndrome reflecting fears about the health and well-being of self and one’s baby, of the hospital and of impending childbirth, and of parenting or the maternal role [6].

Depression during pregnancy shows a worldwide antenatal prevalence of 9% [7], increasing during COVID period from 20 to 31% [8]. In some populations these percentages of anxiety and depression are as high as 65% and 56%, respectively [9]. In addition, these disorders can also manifest jointly [10, 11]. Importantly, both anxiety and depression in pregnancy are associated with postnatal depression and poor maternal–infant bonding after childbirth [12, 13].

Likewise, the negative impact that anxiety and depression during pregnancy can have on both mother and child, due to the increase in the hormone cortisol, has also been demonstrated [14–17]. Some prospective studies relate maternal anxiety to adverse neurodevelopmental outcomes, including cognitive, emotional and behavioral problems [15, 18]. The literature has also associated prenatal anxiety with low gestational weight infants, premature births and arterial hypertension [18].

Pregnancy-related anxiety has also been associated with an increased number of follow-up visits [19], increased tobacco and alcohol consumption [20, 21], and increased likelihood of having a cesarean section and requesting an elective cesarean section [22–24]. Moreover, women who manifested anguish during maternity were more likely to experience a higher risk of experiencing disaffection towards their children and postpartum depression [11, 25]. These factors are especially relevant because they have a negative influence on pregnancy, childbirth and the postpartum period, and affect the way in which women face motherhood and their new role as mothers.

In a very recent study of our group assessing the prevalence of anxiety and depression and their associated risk factors throughout the pregnancy and postpartum process using a new screening for the early detection of mental health problems, we found that the most relevant factors associated with positive screening for antenatal depression or anxiety during pregnancy, that appeared from the first trimester of pregnancy, were systematically repeated throughout the overall gestation, and were maintained in the postpartum period. This results in a sustained impact of anxiety and depression as early as the first weeks of gestation. The result of early screening for anxiety and depression in pregnancy suggests the need for more effective health care pathways, including some early interventions that reduce the overall burden of the childbearing situation, both on the mother herself, and her child consequently, and on the health care system.

### Existing interventions to help women with mental health problems during pregnancy

Despite the high burden of psychiatric disorders affecting pregnancy and childbearing, there is little empirical research on the most effective interventions to reduce it [11, 14]. In this scenario, the treatment of psychiatric disorders during pregnancy becomes even more important, due to all its consequences, given the great increase that has occurred in recent years due to the COVID pandemic.

The few interventional studies are focused on delivery and postpartum, without considering the whole maternity process (pregnancy, delivery, and puerperium) [14, 15]. In this sense, the ideal intervention is in the detection, assessment, and support during the entire maternity process, starting in early pregnancy stage [26]. Likewise, the support of the midwife, the quality of the relationship established with the woman and the level of her involvement in the choices that affect her, empower the pregnant woman, and increase her satisfaction in the maternity process [27].

The National Institute of Clinical Excellence (NICE) guidelines describe two levels of intervention for women with mental health problems: high-intensity interventions to be carried out by a specialized professional, and low-intensity interventions that can be provided by a facilitator, and where self-help materials can be used [26]. One or other type of interventions will be determined according to the problem and/or the mental diagnosis. Therefore, the midwife, within the multidisciplinary team, has a fundamental role not only in the detection of women presenting a perinatal mental health problem, but also in the support and empowerment of these women through low-intensity interventions.

Different types of low-intensity interventions to reduce anxiety during pregnancy have been described. These interventions, through the relaxation of the body and the mind, such as hypnotherapy, yoga, meditation and mindfulness, are considered effective in changing the perception of anxiety during pregnancy. With them, the woman can change the perception of a stressful situation, developing better adapted coping strategies [28]. Different authors conclude that mind and body interventions could be useful for prevent and treat anxiety during pregnancy without adverse effects [28, 29]. However, the literature recommends investigating them with experimental studies, adequate sample measurements and the use of valid tools to measure their impact in the perinatal period [28].

Within this scenario, there are new technologies under development which are capable of promoting positive changes in people's health [30]. *E-health* is a tool that puts technology, informatics and the Internet at the service of health; and *m-health* is defined as the use of mobile, phones and other wireless technology in medical care in a direct, low-cost and engaging manner [31–34]. Their use is growing exponentially all over the world. Current literature recommends the use of *m-health* interventions for the treatment of mood disorders, and emphasizes the need to conduct new research on the results of these interventions in the prenatal period [35].

### Aims

To test the efficacy of a low-intensity intervention led by midwives to improve mental well-being during pregnancy, using an *e-health* application as a support, in primary care centers.

## Design and methods

This will be a two-arm prospective, randomized, parallel-controlled clinical trial. 70 women will be recruited and screened during their pregnancy. Women showing positive scores in an early mental health screening at weeks 12–14 of pregnancy (screening tests: two Whooley questions, two Generalized Anxiety Disorder-2 [GAD-2] questions, self-administered Edinburg Postnatal Depression [EPDS]) will be randomly allocated to an intervention or control group.

If the answer to all four initial questions is negative, we will consider the screening negative. If the answer is positive to any of the four questions, the screening is positive, and it is recommended to administer the EDPS. EDPS is negative if score < 13 or item 10 is negative. EPDS is positive if score < 13 and item 10 positive or ≥ 13. If the answer is positive to any of the four questions, but the EDPS is between 9–13, they are candidates to enter the study.

The usual monitoring of pregnancy control will be carried out at the center (including anamnesis, blood tests, serology and urine tests, among other assessments), regardless of the group. In a first phase (weeks 12–14 of gestation), the following tests will be performed in both groups: EPDS, State Trait Anxiety Inventory (STAI), Symptom Checklist-90-Revised (SCL-90-R), and Temperament and Character Inventory-Revised (TCI-R). The intervention group will receive the usual mentioned follow-up pregnancy monitoring plus an *e*-*health* (virtual reality) intervention. The control group will receive the usual mentioned follow-up pregnancy monitoring, without the *e*-*health* intervention. In a second phase (6 weeks after), the following assessments will be repeated in both groups: EPDS, STAI, and SCL-90. In the case of the intervention group, a questionnaire on the usability of the technology will also be passed. At the end of the pregnancy all women will receive a questionnaire on their satisfaction with the follow-up of their pregnancy, including questions on equipment, accessibility, organization of the consultation and care and competence of the staff (28 questions in total). Providing a control group that receives the same monitoring control establishes whether the technological low-intensity intervention accounts for the results. The involvement of midwives in collaboration with mental health nurses will maximize the translation of research findings into practice.

### Hypothesis

Low-intensity mental health intervention during pregnancy, using *e-health* as a support tool, is effective in reducing of anxiety, depressive symptoms, and improving satisfaction with pregnancy follow-up.

### Outcome measures

The primary outcome measure is possible mental health improvement in pregnant women according to the EPDS, STAI, and SCL-90. Secondary outcome measures will include the TCI-R and the Whooley and GAD-2 questions. Routinary pregnancy monitoring measures will be also evaluated (i.e., anamnesis, blood tests, serology, and urine tests).

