### Sample and sample size

Pregnant women ≥18 years followed in the primary care centers of the Sexual and Reproductive Health Care of Mútua Terrassa, Barcelona (Spain) will be invited to participate. 

There are very few scientific publications on which to base our assumptions about the differences that the intervention will produce in the results of the scales that measure anxiety in pregnant women. In a previous interventional work published using a mindfulness program to evaluate changes in the EDPS scale in pregnant women, the authors report after the program a mean difference between the two groups of study (intervention and control) of -2.56, with a standard error (SE) of 0.72 [36] From that, the standard deviation (SD) has been calculated as: SE=SD/Root(n), so SD=SE*Root(n). In this case, as the n was different in both groups (51 and 45), we use the minimum of both (45), obtaining a joint SD of 4.83. 

Assuming a power of 80% to detect differences in the contrast of the null hypothesis H_0_: μ_1_=μ_2_ by means of a bilateral T-Student test for two independent samples, a significance level of 5%, and assuming a mean difference between both groups of -3.5 and a SD of both groups of 4.83 units, it will be necessary to include 31 women in the non-intervention group and 31 women in the intervention group, totaling 66 patients in the study. Considering that the expected drop-out rate is 5%, it would be necessary to recruit 70 women (35 in each group). 

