### Measures

*Edinburg Postnatal Depression Scale (EPDS)* [38]*.* This self-reported scale consists of 10 items. The participant chooses which of the four possible answers most closely resembles how she felt the previous week. The validity of the scale into Spanish is satisfactory, with a sensitivity of 79% and a specificity of 95.5%. It showed also good reliability with a Cronbach's alpha of 0.87. The scores range between 0 and 30, and results > 13 or < 13 but item 10 positive during pregnancy are considered positive.

*Generalized Anxiety Disorder-2 (GAD-2)*. This is a very quick screening, comprised by two questions strongly related to anxiety disorder symptoms: “Have you felt nervous, anxious or overwhelmed?” and “Have you felt unable to control or stop your worries?”. For this study, answers to each item will be yes/no. This screening tool has shown a good level of sensitivity and specificity in different studies of validation. If the answer is positive to any of the questions (including the Whooley questions, see below), the screening will be positive, and it will be recommended to administer the EDPS.

*State Trait Anxiety Inventory (STAI)* [39]*.* The aim of the STAI questionnaire is to evaluate two independent concepts of anxiety, each with 20 questions. The state dimension evaluates a transitory emotional state, characterised by subjective, consciously perceived feelings of attention and apprehension and hyperactivity of the autonomic nervous system. The trait dimension evaluates an anxious, relatively stable propensity that characterises individuals with a tendency to perceive situations as threatening. The clinical validity of the Spanish scale showed a sensitivity of 0.94 and a specificity of 1. The internal consistency showed a Cronbach's alpha index between 0.83 and 0.90.

*Symptom Checklist-90-R (SCL-90-R)* [40]*.* Questionnaire made up of 90 items that describe a specific psychopathological or psychosomatic disorder. It is divided into somatization, obsession-compulsion, interpersonal sensitivity, depression, anxiety, hostility, phobic anxiety, paranoid ideation, psychoticism and an additional scale. The intensity of each symptom has to be graduated by the subject from 0 (absence) to 4 (maximum annoyance). The evaluation of the Spanish version showed an internal consistency with Cronbach's alpha index of 0.81–0.90.

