## Data analysis

### Quantitative data analysis

Data analysis will be primarily descriptive. Participant flow through the study will be presented following Consolidated Standards of Reporting Trials (CONSORT) guidelines [46]. Descriptive data will be presented by means and SDs; medians and ranges; or percentages with 95% confidence intervals (CIs), as appropriate depending on the data being described. The following will be calculated: (1) percentage of participants meeting eligibility criteria, (2) percentage of individuals consenting to the study, (3) percentage entering the randomisation phase, (4) the number of sessions completed by those in the treatment arm, (5) percentage completing the outcome measures at post-treatment follow-up, (6) between group pre-post effect sizes and CIs on the mental health tests. T-tests, Mann Whitney U tests, and or Wilconxon tests will be used, as appropriated. Quantitative analyses will be performed with the program Statistical Package for the Social Sciences (SPSS) v23.0 (IBM company, Chicago, Illinois, USA). A p < 0.05 will be considered statistically significant.

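### EPDS, STAI and SCL-90 are all primary with no success rule, but the trial is sized for one EPDS test, so 5% error and 80% power cannot both hold

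*Protocol article*

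**What the plan says.** The section Outcome measures reads: "The primary outcome measure is possible mental health improvement in pregnant women according to the EPDS, STAI, and SCL-90". It gives no ranking, no score within an instrument and no rule for combining the three. The abstract (Methods/design) lists the same three as primary and then adds "and the Cambridge Worry Scale (CWS) instruments", which the main text does not mention.

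The instruments differ in structure, according to the section Measures. The EPDS has 10 items and one score running from 0 to 30. The STAI is meant to "evaluate two independent concepts of anxiety, each with 20 questions". Of the SCL-90-R the section says: "It is divided into somatization, obsession-compulsion, interpersonal sensitivity, depression, anxiety, hostility, phobic anxiety, paranoid ideation, psychoticism and an additional scale".

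The section Quantitative data analysis names t-tests and rank tests and sets one threshold: "A p < 0.05 will be considered statistically significant". It gives no adjustment or testing order.

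The section Sample and sample size describes one comparison: "Assuming a power of 80% to detect differences in the contrast of the null hypothesis" of equal means, by a two-sided two-sample t-test at 5%. The difference is 3.5 points and the SD 4.83, the SD being derived from an EPDS result in an earlier mindfulness study. The section Hypothesis claims more than one effect: the intervention "is effective in reducing of anxiety, depressive symptoms, and improving satisfaction with pregnancy follow-up".

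**The concern.** Three sections do not fit together. One test was sized, three or four instruments are primary, and each may be judged at the full 5%. With no success rule, a reader of the results cannot tell what would have counted as failure. A significant result on one instrument, with nothing on the others, could be reported as efficacy, and the choice could be made after the data are seen. If instead the investigators meant that all instruments must improve, the trial is too small for the 80% power it states. The article hopes to bring the intervention into routine primary care, so the weight that one significant scale can bear matters.

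**Working it through.** **Inputs.** From Sample and sample size: difference 3.5, SD 4.83, two-sided 5%, 31 per arm, 5% drop-out. From Outcome measures: three primary instruments; from the abstract: four. From Quantitative data analysis: p < 0.05 per test. Assumed here, because the article gives neither: correlations between instruments of 0 to 0.8, and 80% power for STAI and SCL-90 as well as for EPDS.

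**Step 1: the plan's own figure.** Standardised difference = 3.5 / 4.83 = 0.725. The two-sample t-test needs 30.9 per arm for 80% power, so 31, and power at 31 per arm is 80.2%. The stated 31 reproduces for a single EPDS test.

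**Step 2: any one instrument is enough.** With k independent tests the chance of at least one false positive is 1 − 0.95^k.
- k = 3: 1 − 0.95³ = 1 − 0.857 = 14.3%.
- k = 4 (with the CWS): 1 − 0.95⁴ = 18.5%.

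For correlated instruments I used equally correlated normal test statistics. The last column is the chance of at least one significant result when each instrument has 80% power.

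| Correlation | Error, 3 instruments | Error, 4 instruments | Power, any of 3 |
|---|---|---|---|
| 0 | 14.3% | 18.5% | 99% |
| 0.5 | 12.5% | 15.6% | 95% |
| 0.7 | 10.9% | 13.0% | 92% |
| 0.8 | 9.8% | 11.4% | 90% |

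If only the EPDS has 80% power, the any-of-three rule still has at least 80%. This reading loses the 5% and keeps the power.

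**Step 3: all three are required.** The error rate is at most 5%. Joint power if independent is 0.80³ = 51.2%. At correlations 0.5, 0.7 and 0.8 it is 61%, 66% and 69%. This reading keeps the 5% and loses the power.

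**Step 4: what repair by adjustment or re-sizing would take.** These figures use the EPDS difference and SD for every instrument.
- Bonferroni over three: 0.05 / 3 = 0.0167 per test. Power at 31 per arm falls to 65.2%. Restoring 80% needs 42 per arm, that is 84 evaluable and 84 / 0.95 = 88.4, so 89 recruited.
- All three required at 0.05: each test needs power 0.80^(1/3) = 92.8% if independent, hence 46 per arm.

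**Step 5: is the EPDS measured at 6 weeks in both arms?** Design and methods repeats EPDS, STAI and SCL-90 in both groups at the second phase. Control group lists STAI, SCL-90 and TCI-R at the extra visit and repeats those scales, without the TCI-R, 6 weeks later; the EPDS is not among them. Screening may supply a baseline EPDS, but it does not supply the 6-week value in controls.

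**The case against.** **A separate analysis plan may hold the rule.** The adjustment method, the testing order and the choice of subscale are often left to it, and their absence here is no fault. That stands. But which outcome is primary, and which outcome the sample size serves, are fixed in this article, and they disagree. An adjustment added later would also contradict a sample size that spends the whole 5% on one test.

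**The analysis is described as mainly descriptive, with effect sizes and intervals.** True, and the threshold sentence is generic. Yet the aim is to test efficacy, the hypothesis is directional, the sample size is built on a null-hypothesis test, and a significance level is declared. The article presents a confirmatory trial.

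**Stronger readings that the article does not support.**
- A reader might infer that the plan has neither 5% error nor 80% power. Each reading breaks one of the two and keeps the other, and for the EPDS alone both are right.
- A reader might count 1 EPDS, 2 STAI and 10 SCL-90-R scores and put the error at 1 − 0.95¹³ = 48.7%. Separate testing of every score would raise the error further, but the article does not say that it will be done. Nor are all three instruments multi-scale: the EPDS has one total.
- A reader might take the Hypothesis as requiring all three instruments. It names satisfaction, which is not a primary outcome, and does not name the SCL-90, so it does not fix that rule.

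**The Bonferroni figures depend on the inputs.** They do. With 33 evaluable per arm (35 less about 5%), power is 82.6% for a single test and 68.6% under Bonferroni. The SD of 4.83 is also taken as stated; if 0.72 is the standard error of the between-group difference, the SD would be 0.72 / √(1/51 + 1/45) = 3.52 and power would be higher. These are separate questions and do not alter the error rates in Step 2.

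**Conclusion.** The point holds in this form: the primary set, the single threshold and the sample size do not belong to the same design, so the stated 5% and 80% cannot both apply to the primary objective. If any of three instruments suffices, the error is about 10% to 14% over correlations of 0.8 to 0, and up to 18.5% with the abstract's fourth instrument. If all three are needed, joint power is about 51% to 69%. The error figures rest on the assumed correlations. The joint-power figures rest also on 80% power for STAI and SCL-90, for which the article gives no effect size or SD. The conflict between abstract and main text over the CWS, and the missing EPDS in the control-group schedule, need no assumption.

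**What to change.** 1. In the abstract and in Outcome measures, name one primary outcome: the between-arm difference in EPDS total at the 6-week assessment, two-sided 5%. It is the only outcome with a sample-size basis.
2. Make STAI and SCL-90 secondary, with named scores tested in a fixed sequence or by Holm's method, and only after the EPDS test is significant. Do the same for the CWS if it is really collected; otherwise remove it from the abstract.
3. Report everything else as estimates with 95% confidence intervals, and limit the p < 0.05 sentence to this hierarchy.
4. Reconcile Control group with Design and methods on whether controls complete the EPDS at 6 weeks.

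**Cost.** The first three steps are wording and keep the stated 31 per arm, 5% and 80%. The fourth is wording too if controls do complete the EPDS; if they do not, an assessment must be added. All of it should be settled before outcome data are seen. The real price is that a significant STAI or SCL-90 result alone no longer counts as success, which is not trivial because the article describes the application as meant to reduce anxiety. If the investigators want several primary instruments, the alternative is a stated any-or-all rule with re-sizing. On EPDS assumptions that means about 42 per arm under Bonferroni over three, or 46 per arm if all three must succeed and are independent; STAI and SCL-90 would need effect sizes and SDs of their own.

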### Control group

Pregnant women in the control group will be cited for an extra visit, where they will be given the following scales: STAI, SCL-90 and TCI-R. These women will undergo the usual monitoring of pregnancy control at the center by the midwife, according to the Protocol for Monitoring Pregnancy of the Generalitat de Catalunya [45]. The women will be called to back after 6 weeks to go through the same scales again (except the TCI-R), and the pregnancy satisfaction questionnaire.

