**Fig. 1 Fig1:**
[figure not shown]
Modules forming the *m-health* virtual reality intervention

The intervention will occur off site using the wireless technology. The aspects that conform this intervention will be: information about the most common perinatal mental health problems, exercises based on attention to breathing (mindfulness—relaxation), 6 weeks of duration, for 14 min a day, knowledge from involved personnel of the number of times the woman has connected and the time she has done the exercise, satisfaction questions to pregnant women after pregnancy, alerts to notify the principal investigator if there is a problem with *e-health*, and, finally, an email address to contact the principal investigator. This intervention has been previously evaluated by a committee of eight experts. These experts gave their recommendations to improve the virtual application. Once the changes were applied, a pilot test was conducted with five women who reported the level of ease of viewing, using and manipulating the application.

Specifically, the virtual application will consist of an adaptation to pregnant women of an application for the general public. The main character that appears in the application is a female avatar, who talks about questions aimed at the target group of pregnant women.

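### None of the three named secondary outcomes is scheduled after the intervention, while satisfaction, which the hypothesis claims, is in neither outcome list and has conflicting time points

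*Protocol article*

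**What the plan says.** **Secondary outcomes.** Outcome measures reads: "Secondary outcome measures will include the TCI-R and the Whooley and GAD-2 questions". The abstract gives the same three measures.

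**Assessment schedule.** Design and methods places the TCI-R in the first phase, at weeks 12–14, together with EPDS, STAI and SCL-90-R. For follow-up it says: "In a second phase (6 weeks after), the following assessments will be repeated in both groups: EPDS, STAI, and SCL-90". The same section introduces the other two measures as "screening tests: two Whooley questions, two Generalized Anxiety Disorder-2 [GAD-2] questions". The recruitment section makes a yes to at least one of those four questions a condition of candidacy.

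**Control arm.** The Control group section says that these women will be "called to back after 6 weeks to go through the same scales again (except the TCI-R), and the pregnancy satisfaction questionnaire".

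**Satisfaction.** The Hypothesis section states that the intervention "is effective in reducing of anxiety, depressive symptoms, and improving satisfaction with pregnancy follow-up". On timing, Design and methods says: "At the end of the pregnancy all women will receive a questionnaire on their satisfaction with the follow-up of their pregnancy". The description of the intervention, after Fig. 1, lists among its components "satisfaction questions to pregnant women after pregnancy". The Measures section describes a 28-item satisfaction questionnaire with an overall score and two cut-offs.

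**The concern.** A measure can serve as an efficacy outcome only if it is taken after treatment has had a chance to act. As scheduled, the TCI-R, Whooley and GAD-2 are all taken before the intervention. A difference between arms on any of them would describe chance imbalance at entry, not an effect of the virtual reality programme. A reader of the eventual report would expect secondary results on these measures, and the plan cannot supply them.

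Satisfaction has the opposite problem. The trial intends to claim an effect on it and has an instrument for it, but does not list it as an outcome, so its place among the trial's claims is not fixed in advance. Its timing is also stated inconsistently. If the two arms rate their care at different stages of pregnancy, a difference in score could come from the stage and not from the intervention. No analysis could separate the two, because timing and arm would coincide.

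**Working it through.** The plan gives no figure to reproduce on this point. The check sets the article's statements side by side.

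**Step 1: are the named secondary outcomes measured after the intervention?**

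| Measure | Before the intervention | Six-week assessment | Source |
|---|---|---|---|
| TCI-R | Yes, first phase | No, expressly excluded | Design and methods; Control group |
| Whooley | Yes, entry screen | Not scheduled | Design and methods; recruitment section; Measures |
| GAD-2 | Yes, entry screen | Not scheduled | Design and methods; recruitment section; Measures |
| EPDS, STAI, SCL-90 (primary) | Yes | Yes, both arms | Design and methods |

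Count of named secondary outcomes with a scheduled post-intervention value: 0 of 3.

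Two other places might have supplied one. Data collection and management names a post-intervention time point but no instruments. Fig. 2 is not available in the text reviewed; its legend expands only EPDS, SCL-90, STAI and TCI-R. Neither supports a repeat of the Whooley or GAD-2 questions.

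**Step 2: is satisfaction listed?** The hypothesis has three elements: anxiety, depressive symptoms and satisfaction with follow-up. The abstract's outcome list and the Outcome measures section both omit satisfaction: 0 of 2 lists.

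**Step 3: when is satisfaction measured?**

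- Design and methods: all women, end of pregnancy.
- Control group: controls, at the six-week recall.
- Intervention description: some satisfaction questions after pregnancy, instrument not named.

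The first two contradict each other for the control arm. The third is ambiguous.

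**Step 4: how far apart could the arms be?** This applies only if controls follow the Control group text and intervention women follow Design and methods. The six weeks can be counted from two starting points:

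- from the first phase at weeks 12–14: 12 + 6 = 18 to 14 + 6 = 20 weeks;
- from the extra visit at weeks 15–17: 15 + 6 = 21 to 17 + 6 = 23 weeks.

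The controls' rating would then fall between weeks 18 and 23. The article gives no week for the end of pregnancy. Assuming 37 to 40 weeks, the gap runs from 37 − 23 = 14 to 40 − 18 = 22 weeks. This illustrates one reading; it is not a property of the design as a whole.

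**The case against.** The strongest reply is that this is largely a matter of labels. The hypothesis on anxiety and depressive symptoms is tested by EPDS, STAI and SCL-90, which are taken before and after in both arms. The three secondary measures were never needed for that test. This is correct, and it limits the consequence. A reader might infer that the trial cannot test its main claims; the documents do not support that, because the primary comparisons are untouched by this point.

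A second reply concerns timing. Design and methods is the overall design statement, it covers both arms, and it sets the end of pregnancy for all women. The Control group section is a loose summary: its list of scales omits the EPDS, which Design and methods gives to both groups. On this view the control text is a drafting slip and there is no confounding. That may be so, but the article does not say which text governs, and staff running the control visits could reasonably follow the section written for that arm.

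Two further inferences are tempting and go too far. One is that satisfaction is timed in three different ways. The phrase in the intervention description does not name the 28-item questionnaire and may refer to satisfaction with the application; if it does mean the questionnaire, after pregnancy is close to the end of pregnancy. The other is that the satisfaction question cannot be answered at all. That would follow only if the statement in Design and methods were set aside for one arm.

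It could also be said that an analysis plan or full protocol would settle the matter. An analysis plan cannot analyse values that are not collected, and the finding rests on an explicit list of repeated scales, an explicit exclusion of the TCI-R and two conflicting time points, not on the article's silence. Finally, the entry rule requiring at least one yes would not by itself prevent the Whooley and GAD-2 questions from serving at follow-up; what prevents it is that they are not asked again.

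**Conclusion.** The point holds in two parts. First, 0 of the 3 named secondary outcomes has a scheduled post-intervention assessment, so none can show a treatment effect as planned. This rests on the schedule as written and needs no numerical assumption. Second, satisfaction is one of three hypothesised effects, is in neither outcome list, and has contradictory timing for the control arm. The resulting confounding is conditional: it arises if controls are assessed at the six-week recall and intervention women at the end of pregnancy, and it disappears if Design and methods is followed in both arms. The illustrative gap of 14 to 22 weeks depends on that reading and on an assumed end of pregnancy at 37 to 40 weeks. The primary comparisons are not affected. The matter should be corrected, but it does not undermine the trial's main test.

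**What to change.** 1. In Outcome measures and the abstract, reclassify the TCI-R, Whooley and GAD-2 as baseline or screening variables. If the Whooley and GAD-2 are wanted as outcomes, ask the four yes/no questions again at the six-week assessment in both arms.
2. List the 28-item overall satisfaction score as a secondary outcome.
3. Reconcile Design and methods with Control group so that the satisfaction questionnaire is given at one common time point in both arms. The end of pregnancy, which Design and methods already plans for all women, would serve; the questionnaire would then be removed from the controls' six-week recall.
4. In the intervention description, say whether the satisfaction questions mean this questionnaire or satisfaction with the application.

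The cost is mainly wording. Re-asking four short questions adds little to a visit that is already planned. Moving the controls' questionnaire to the end of pregnancy may lose some responses, since fewer controls may return it then than at the six-week recall.
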